|------------------------------------|---------------------------------------------------------------------------------------------------------------------------------------------------------------------------------------------------------------------------------------------------------------------------------------------------------------------------------------------------------------------------------------------------------------------------------------------------------------------------------------------------------------|
|                                    | 
registration in the trial;
 
 
- Before patient registration, written consent must be given according to ICH/GCP, national and local regulations.
 
 
Exclusion criteria:
 
 
- History of allergy to iodine, shellfish or ICG;
 
- Pregnant or lactating woman;
 
- Any condition that in the opinion of the investigator could potentially jeopardize the health status of the patient.
 
 |
| Planned trial interventions | 
In addition to standard-of-care, patients will receive an intravenous injection of 10 mg ICG 24 prior to surgery. During surgery, patients undergo a SL, whereupon inspection, LUS and NIR fluorescence imaging will be performed. A biopsy will be taken from any suspect lesions. Decision to continue the resection is up to the surgeon. Follow-up will last at least 6 months.
                                                                                                                    |
| Statistical design          | 
Using A'Hern's single stage phase II trial design and <math>\alpha=0.05</math> and power=80%, 25 patients are needed to distinguish between an averted laparotomy rate of 30% (worth exploring in a phase III trial) and 10% or less (unacceptable outcome). Therefore, a total of 25 patients will be included. This requires at least 6 averted laparotomies to reach the positive endpoint.
                                                                                                         |

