### 3 Background

Pancreatic cancer has a very dismal prognosis. Surgery offers the sole chance of long-term survival. However, the presence of metastatic disease in pancreatic cancer patients limits surgical interventions. Even after extensive preoperative assessment, up to 38% of patients undergoing laparotomy with curative intent turn out to have incurable disease, for example due to metastases or an unresectable primary tumor (1). All current preoperative imaging modalities, including CT and MRI, have limited sensitivity in detecting the typically very small peritoneal implants and superficial liver metastases of pancreatic cancer. In a disease with such a poor prognosis, it is important to spare patients with incurable disease the morbidity, inconvenience and expense of a futile operation. Therefore, staging laparoscopy (SL) is being advocated in literature in selected patients (2). However, it has not yet been implemented in clinical guidelines; each individual surgeon has to apply his or her threshold as to whether SL is indicated. One of the aims of this study is to design a clinical protocol for SL that fits in the clinical pathway of patients with pancreatic and periampullary cancer.

The yield of SL depends on the quality of preoperative imaging and the inherent likelihood of metastatic disease (3). In addition, sensitivity of SL can be amplified by adding laparoscopic ultrasonography (LUS) and near-infrared (NIR) fluorescence imaging (4). When no metastatic lesions are found, ultrasonic examination of the whole liver, lymph nodes and superior mesenteric artery can be readily performed. NIR fluorescence imaging using indocyanine green (ICG) is a relatively easy method that can be used to identify metastases in the liver. The hepatic clearance of ICG enable identification of liver tumors, but do not allow detection of metastases located elsewhere. Yokoyama et al. have shown that NIR fluorescence imaging during open surgery identified micrometastases in the liver in 16% (8 of 49) of patients with pancreatic cancer (5). Importantly, abnormal fluorescence of at least 1.5 mm in greatest diameter was highly predictive for manifestation of hepatic metastases within 6 months: 77% (10 of 13) of patients developed hepatic metastases, compared to 3%

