(1 of 36) of patients without abnormal fluorescent lesions. Our group showed feasibility of NIR fluorescence imaging of colorectal cancer liver metastases during open surgery (6) and of uveal melanoma liver metastases during laparoscopic procedures (7).

Presently, the only blood-based biomarkers for diagnosis, prognosis and monitoring of treatment in pancreatic patients are measurements of carbohydrate antigen 19-9 (CA19-9) and carcinoembryonic antigen (CEA), but these are not very specific (8). Circulating tumor cells (CTCs) are cells that have detached from the primary tumor, entered the blood circulation and may lead to distant metastases (9). Characterization of CTCs, including analyzing KRAS mutations, may result in further insight into the clinical implications of CTC detection in pancreatic cancer patients.

This study will be the first to combine SL, LUS and NIR fluorescence imaging and aims to determine the added value of these three imaging techniques in patients with pancreatic and periampullary cancer undergoing resection with curative intent. In addition, we aim to identify predictors for patients that may benefit from SL and to design a clinical protocol for SL that fits in the clinical pathway.

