In case no metastases are identified, the surgical procedure will continue, either laparoscopic or via laparotomy. In the validation phase of the laparoscopic fluorescence, the liver will be assessed again with the validated open fluorescence imaging system once the laparotomy has been performed (6). When metastases are identified, the decision to continue the resection of the primary tumor is up to the surgeon. When only NIR fluorescence imaging identifies one or more metastases, the procedure will continue, as the clinical significance of these lesions is yet unknown. Reference for final diagnosis of lesions will be histopathological examination at the pathology department. Furthermore, ascetic fluid will be collected in 3 regions: near the duodenum, the ligament of Treitz and the cavum of Douglas. These samples will be analyzed for tumor cells, similar to the EXPECT study.

Follow-up will occur according to the current local standard protocol, including a visit every three months to the outpatient clinic of surgery in conjunction with the department of oncology. Visit. In short, this includes an outpatient visit to the clinic of surgery every three months. A CT-scan will be performed only in case locoregional or metastatic disease is suspected. Radiologic findings, hematology (e.g. CTCs CA19-9, CEA-mRNA levels), pathology, ascetic fluid etc. will be collected to identify predictors for patients who may benefit from SL.

Risk stratification will be done by stage groups of the tumor and CA19-9 levels.

[figure not shown]

**Figure 1.** Flow diagram of study. LUS: laparoscopic ultrasonography; PA: pathology; RFA: radiofrequency ablation; CT: computed tomography.

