### **6.2 Secondary outcomes**

- Sensitivity and positive predictive value of laparoscopic inspection vs. LUS vs. NIR fluorescence imaging vs. histopathological examination.
- Positive and negative predictive value of LUS vs. NIR fluorescence imaging on the occurrence of distant metastases.
- Distant disease-free survival (occurrence of distant metastases)
- Overall survival
- Perioperative morbidity and mortality.
- Duration of surgical procedures.

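### Section 6.2 sets no time horizon for the predictive values of LUS and NIR, and its target includes sites that NIR cannot image

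*Protocol*

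**What the plan says.** Four parts of the protocol bear on this point.

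- **Outcome (6.2 Secondary outcomes):** "Positive and negative predictive value of LUS vs. NIR fluorescence imaging on the occurrence of distant metastases". Any distant site counts, and no time point is given. Distant disease-free survival is a separate item in the same list.
- **Length of follow-up (2 Summary, planned trial interventions):** "Follow-up will last at least 6 months". This is a floor, with no upper limit and no common cut-off.
- **How later metastases are found (4 Study design):** all patients follow the local standard, and "this includes an outpatient visit to the clinic of surgery every three months". Imaging is conditional: "A CT-scan will be performed only in case locoregional or metastatic disease is suspected". Histopathology is the reference for lesions. No separate reference is named for metastases that appear later.
- **The precedent (3 Background):** in an open-surgery study, abnormal fluorescence of at least 1.5 mm "was highly predictive for manifestation of hepatic metastases within 6 months: 77% (10 of 13) of patients developed hepatic metastases", against 3% (1 of 36) of patients without such lesions. The same section says that hepatic clearance of ICG reveals liver tumours but not metastases at other sites.

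**The concern.** A predictive value for a future event is defined only once the period for that event is fixed. Here one patient may contribute 6 months and another much longer, and both enter the same proportion. If follow-up closes on one calendar date, which the protocol neither states nor excludes, the earliest patients are watched longest, and the result depends partly on the pace of enrolment.

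The target is a second problem. Scoring NIR on any distant metastasis charges it with failures at sites where, by the protocol's own account, it cannot see. A fluorescence-negative patient who later develops, say, a lung metastasis lowers the NPV of NIR but says nothing about its reading of the liver.

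This outcome matters more than its place in the list suggests. Section 4 lets surgery proceed when NIR alone is positive, because the clinical meaning of such lesions is not yet known. Later metastasis is the evidence that would show that meaning. As 6.2 is worded, the result could not be set beside the cited 77% and 3%, which concern the liver and 6 months.

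**Working it through.** **1. The protocol's cited figures (section 3).**
- PPV at 6 months = 10/13 = 76.9%, matching the stated 77%.
- Event rate without abnormal fluorescence = 1/36 = 2.8%, matching the stated 3%. NPV at 6 months = 35/36 = 97.2%.

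**2. Effect of the horizon.** The direction needs no model: the cumulative share with a metastasis cannot fall over time, so PPV cannot fall and NPV cannot rise. The size needs an assumption. Take a constant hazard in each group and complete detection. Then

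PPV(t) = 1 − (3/13)^(t/6) and NPV(t) = (35/36)^(t/6), with t in months.

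| Horizon | PPV | NPV |
|---|---|---|
| 6 months | 76.9% | 97.2% |
| 12 months | 1 − (3/13)² = 94.7% | (35/36)² = 94.5% |
| 24 months | 1 − (3/13)⁴ = 99.7% | (35/36)⁴ = 89.3% |

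NPV moves more if the event rate in test-negative patients is higher. With an assumed 15% at 6 months, NPV is 85.0% at 6 months, 0.85² = 72.2% at 12 and 0.85⁴ = 52.2% at 24.

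**3. Mixed follow-up.** If half the patients in each group were followed for 6 months and half for 12 (assumed), the pooled values would be (76.9 + 94.7)/2 = 85.8% for PPV and (97.2 + 94.5)/2 = 95.9% for NPV. These describe neither horizon.

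**4. Detection only on suspicion.** Observed PPV = true PPV × share detected. Observed NPV = 1 − (true event rate in test-negatives × share detected). All detection shares here are assumed.
- If 50% to 100% of events in test-positives are found, observed PPV is 0.769 × 0.5 = 38.5% up to 76.9%.
- If the true rate in test-negatives is 20% and 40% to 100% are found, observed NPV is 1 − 0.20 × 0.4 = 92% down to 80%.

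Incomplete detection therefore lowers PPV and raises NPV. No detection share can be taken from the protocol.

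**5. What is not touched.** The primary design reproduces. For at least 6 of 25, the exact binomial gives a one-sided alpha of 0.033 at a rate of 10% and power of 0.807 at 30%. 25 is the smallest number that meets alpha ≤ 0.05 and power ≥ 80%. The predictive values do not enter this calculation.

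**The case against.** **An SAP could set the window.** Only the protocol is at hand, and the planned minimum follow-up already covers the 6 months of the precedent. This stands for the handling of death as a competing event and for interval-censoring in distant disease-free survival, which are SAP matters and no part of this point. It does not dispose of the rest. Section 6.2 itself names the target, and that target conflicts with what section 3 says NIR can image. Nor could an SAP recover the reason for a CT that was never recorded.

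**Any distant metastasis is a defensible patient-level target.** LUS also examines lymph nodes and vessels, and the protocol plans no formal comparison with 77% and 3%. That is fair, and is why any distant metastasis should stay as a supportive outcome.

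**The estimates will be imprecise anyway.** At the precedent's positivity, 25 × 13/49 = 6.6, so about 7 patients would be NIR-positive. A PPV of 5/7 has an exact 95% interval of about 29% to 96%, wider than the shift from 77% to 95%. This limits the practical weight, but it is no reason to leave the quantity undefined.

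**A stronger reading that the text does not support.** A reader might infer that the team, knowing the LUS and NIR results, will scan image-positive patients more often and so make an uninformative signal look predictive. For example, assume a true risk of 40% in both groups, with 90% detected in positives and 50% to 60% in negatives. Observed risks are then 36% against 20% to 24%, a ratio of 1.8 to 1.5. Every one of those inputs is assumed, and with equal detection the ratio is 1.0. The protocol does not say that test results prompt scans, nor that those ordering them are unaware of the results. All patients have the same three-monthly visits.

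**Unseen material.** Figure 1 is not shown and its legend lists CT, so a timed scan there cannot be excluded. The text of section 4, however, restricts follow-up CT to suspected disease.

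**Conclusion.** The point holds for the outcome definition. Section 6.2 fixes PPV and NPV badly: there is no horizon, follow-up is only a minimum, and the target includes sites NIR cannot image. The direction of the dependence on follow-up is certain. The size given, 77% to 95% for PPV and 97% to 95% for NPV between 6 and 12 months, rests on a constant hazard, complete detection, and figures borrowed from an open-surgery study of liver metastases.

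Unequal detection by test result is possible but not shown, and the protocol gives no basis for sizing it. It should not be reported as an established bias. The issue concerns a secondary outcome; the averted-laparotomy outcome, its decision rule and the 25 patients are unchanged. Accuracy against histopathology, the first item in 6.2, is a separate outcome and does not depend on follow-up CT.

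**What to change.** In section 6.2:

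1. Define PPV and NPV at 6 months from surgery for every patient. The minimum follow-up already supports this, and the precedent used the same horizon.
2. Make liver metastases the outcome for the LUS/NIR comparison, and keep any distant metastasis as a supportive outcome.
3. Describe the outcome as clinically manifest metastases, because CT follows suspicion.
4. Record the date of and reason for each follow-up CT, and report CT use by LUS and NIR result.

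The cost is a change of wording and a small addition to the case report form; no scans are added. For that reason item 4 makes unequal detection visible but does not remove it. The downside of item 1 is that metastases after 6 months no longer enter PPV and NPV and appear only in distant disease-free survival.

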## **5 Objectives**

### **5.1 Main objective**

- To determine if SL, LUS and NIR fluorescence imaging can reduce the laparotomy rate in patients with pancreatic or periampullary cancer planned to undergo resection with curative intent.

### **5.2 Secondary objectives**

- To identify predictors for patients that may benefit from SL.
- To design a clinical protocol for SL that is feasible in the current clinical pathway.

## **6 Outcomes**

### **6.1 Main outcomes**

- Percentage of averted laparotomies.

### **6.2 Secondary outcomes**

- Sensitivity and positive predictive value of laparoscopic inspection vs. LUS vs. NIR fluorescence imaging vs. histopathological examination.
- Positive and negative predictive value of LUS vs. NIR fluorescence imaging on the occurrence of distant metastases.
- Distant disease-free survival (occurrence of distant metastases)
- Overall survival
- Perioperative morbidity and mortality.
- Duration of surgical procedures.

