#### **4 Study design**

All patients planned to undergo explorative or curative surgery for pancreatic or periampullary cancer can be included, provided that they meet the inclusion criteria and none of the exclusion criteria. All patients will receive standard-of-care. This includes a CT-scan < 1 month prior to surgery. Optional imaging, such as (endoscopic) ultrasonography, MRI and FDG-PET, may also be performed if required. In addition, peripheral blood samples (8 mL) will be taken from patients before surgery or chemotherapy. These samples will be analyzed for CTCs, CEA, CA19-9 and bilirubin levels. Patients will receive up to three days before surgery an intravenous injection of 4 ml 2.5 mg/ml ICG (10 mg ICG in total).

The SL procedure starts with visual inspection. The laparoscope is inserted via a subumbilical 10 mm trocar. A second 10 mm port is inserted along the anticipated laparotomy incision to allow LUS under direct vision. Up to two additional 5 mm ports may be necessary to allow exposure of organs and potential palliative surgery. The whole abdomen is inspected, including the parietal and visceral peritoneum, the pelvis, the liver, the porta hepatitis, the gastrohepatic omentum, the duodenum, the transverse mesocolon and celiac region. Secondly, LUS (with or without Doppler) of the primary tumor, liver, portal vein, hepatic artery, lymph nodes and superior mesenteric artery will be performed. NIR fluorescence imaging of the liver surface will be performed lastly. Fluorescence will be divided into rim, partial, full and nonspecific (i.e. artefacts) pattern. Any lesions likely to be metastases are sampled and analyzed, either via a biopsy or via radical resection. In case of multiple lesions with similar appearance on inspection, ultrasound and fluorescence, only one biopsy has to be performed when LUS shows a similar signal in all these lesions. However, when one or more lesions are found solely by NIR fluorescence imaging, multiple small biopsies have to be performed to confirm the diagnosis.

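### The follow-up predictive values of LUS and NIR are scored only against distant metastases with no site restriction, although NIR examines only the liver; a liver-specific version is needed to show what a fluorescent liver lesion means

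*Protocol*

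**What the plan says.** Among the secondary outcomes in Protocol section 6.2 is "Positive and negative predictive value of LUS vs. NIR fluorescence imaging on the occurrence of distant metastases". No organ and no time window is attached. Distant disease-free survival, in the same list, uses the same unrestricted event. The section contains no liver-specific follow-up outcome.

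The two techniques examine different fields. Section 4 says "NIR fluorescence imaging of the liver surface will be performed lastly". Of LUS it says "Secondly, LUS (with or without Doppler) of the primary tumor, liver, portal vein, hepatic artery, lymph nodes and superior mesenteric artery will be performed". Section 3 gives the reason for the narrow NIR field: "The hepatic clearance of ICG enable identification of liver tumors, but do not allow detection of metastases located elsewhere".

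The clinical evidence cited in section 3 is hepatic and has a time window: abnormal fluorescence of sufficient size "was highly predictive for manifestation of hepatic metastases within 6 months". The counts given are 10 of 13 patients with such lesions and 1 of 36 without.

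Section 4 lets the operation proceed when only NIR finds lesions, "as the clinical significance of these lesions is yet unknown". The Summary (section 2) sets follow-up at a minimum of 6 months. Under section 4, a CT scan during follow-up is made only when recurrence is suspected.

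**The concern.** A test confined to one organ is scored against an event that can happen in any organ. Suppose a patient has no liver fluorescence, the liver stays clear, and peritoneal metastases appear later. Scored as written, that patient is an NIR false negative, although the liver reading was correct. Conversely, an extrahepatic recurrence in a patient with liver fluorescence but no liver metastasis turns a false positive into a true positive. Extrahepatic spread is a realistic possibility here: section 3 names peritoneal implants beside superficial liver metastases as the disease that imaging tends to miss.

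At stake is the reading of one secondary outcome. It is the listed outcome that links an NIR result to later disease, and the protocol itself says that the meaning of NIR-only lesions is unknown. With any-site scoring alone, the value mixes the performance of NIR in the liver with the frequency of spread elsewhere. It also cannot be set beside the hepatic rates that the protocol cites. The comparison with LUS is uneven as well, because LUS looks beyond the liver and section 6.2 does not say which LUS findings count as positive.

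**Working it through.** **1. The cited figures (section 3).** 10/13 = 76.9% (stated as 77%) and 1/36 = 2.8% (stated as 3%). They reproduce, and 13 + 36 = 49 matches the cited cohort size. With hepatic metastasis as the event:

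- PPV = 10/13 = 76.9%
- NPV = 35/36 = 97.2%

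**2. Direction, without assumptions.** Every hepatic metastasis is also a distant metastasis. For the same patients and follow-up, widening the event can only move patients from no event to event. The number of events among NIR-positive patients cannot fall, so PPV is equal or higher. The number of event-free NIR-negative patients cannot rise, so NPV is equal or lower. On the cited data, each extrahepatic recurrence in a patient without liver metastasis adds 1/13 = 7.7 points to PPV or takes 1/36 = 2.8 points off NPV, depending on the NIR result.

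**3. Size, with an assumption.** Let e be the proportion of patients without hepatic metastasis who develop an extrahepatic distant metastasis. The protocol gives no value. I assume the same e whatever the NIR result.

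- PPV, any site = (10 + 3e)/13
- NPV, any site = 35(1 − e)/36

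| e (assumed) | PPV | Change | NPV | Change |
|---|---|---|---|---|
| 0 (hepatic event) | 76.9% | – | 97.2% | – |
| 10% | 79.2% | +2.3 points | 87.5% | −9.7 points |
| 20% | 81.5% | +4.6 points | 77.8% | −19.4 points |
| 30% | 83.8% | +6.9 points | 68.1% | −29.2 points |

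The liver performance of NIR is identical in every row; only the event definition changes. If e differed by NIR result, each formula would hold with its own e, so independence matters only for reading PPV and NPV off the same row.

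**4. Precision at this trial's size.** If the cited split applied to 25 patients (an illustration only), there would be 25 × 13/49 = 6.6 NIR-positive and 25 × 36/49 = 18.4 NIR-negative patients. Exact 95% intervals for plausible results are 29% to 96% for 5/7 and 73% to 99.9% for 17/18. The PPV shift in the table is small beside such an interval. The NPV shift, at the upper end of the assumed range, is about as large as the whole interval.

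**The case against.** The strongest reply is that distant metastasis at any site is a legitimate event. The trial wants to spare patients with incurable disease a futile operation, and for that purpose it is useful to know whether a patient with a given LUS or NIR result will develop distant metastases anywhere. A low any-site NPV would truthfully say that a clear liver does not exclude spread. This stands. A reader might infer that the outcome in section 6.2 is simply an error, or that its values are meaningless. The protocol does not support that: section 6.2 does not claim to measure liver accuracy, and the values keep their meaning as general prognosis.

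Four further points stand in part:

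- Follow-up is not the only evidence on NIR-only lesions. Section 4 requires multiple biopsies of them, histopathology is the reference for the final diagnosis, and section 6.2 separately lists sensitivity and PPV against histopathology. These show whether a lesion is malignant; they do not show what a positive or negative NIR result means for later disease.
- It is tempting to call the liver reading wrong whenever a fluorescent lesion is not followed by liver metastasis. That is unsafe. Section 4 allows a suspect lesion to be sampled by radical resection, so a confirmed liver metastasis may be removed and never reappear. Purely hepatic follow-up scoring would make it a false positive.
- The size rests on an extrahepatic rate, and an independence assumption, that the documents do not supply.
- No threshold or decision rule is attached to this outcome, so the inference that NIR would be dismissed because of a poor NPV has no basis in the protocol.

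One might also leave the definition to a statistical analysis plan. But section 6.2 already names the event, and a plan that followed it would inherit the mismatch.

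**Conclusion.** The concern holds in a limited form. As the only follow-up version of these predictive values, any-site distant metastasis does not isolate what a liver finding means, and the protocol's own statements about NIR show why. The direction is certain: as a measure of the liver finding, NPV can only be lowered and PPV only raised, if they change at all. The size is an illustration: with an assumed extrahepatic rate of 10% to 30%, independent of the NIR result, NPV falls from 97% to between 88% and 68%, and PPV rises from 77% to between 79% and 84%. NPV carries the point; the PPV effect is modest.

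This is an inexpensive improvement to one secondary outcome, not a flaw in the trial's main question. The primary outcome (averted laparotomies) and the sample size of 25 do not depend on it.

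**What to change.** In section 6.2, make the main version of this outcome the PPV and NPV of the **liver findings** of LUS and NIR for **hepatic metastases within a stated window**. Six months is a natural choice, since it matches both the cited study and the minimum follow-up. In addition:

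- Record the site or sites of each metastasis.
- Count liver metastases confirmed by histology at surgery, including resected ones, as true positives, or report them separately.
- Keep distant metastases at any site as a separate result, labelled as prognostic.

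This is a change of wording plus one data item, and the site can be read from imaging already made when recurrence is suspected. No extra patients or procedures are needed. There are two costs. Fewer events will count, so intervals that are already wide at 25 patients may rest on fewer positive outcomes. And because the liver is imaged only on suspicion, a clear liver will often be unverified, so comparison with the cited 77% and 3% stays limited even after the change.
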